### Data management and statistical analysis

#### Sample size selection

The primary endpoint is the mRS, measured at 3 months and 1 year after the stroke. Based on data from a pilot study, we assume a prevalence of independence of 51%, dependence of 30% and death of 19%. Several simulations were performed by varying the frequency of exposure to the risk factor studied (very rare to very common). By fixing the risk of first species at 5% and the power of the association test at 80%, to show an odds ratio of at least 2 (odds ratios to move to a higher class: independence to dependence or death, dependence on death), 368 patients should be included to cover a change in exposure to the risk factor studied, ranging from 20% (rare exposure) to 80% (frequent exposure).

The study is stratified on the NIHSS score assessed at inclusion (at the end of the hospital stay for acute episode management) in 3 categories (≤6, 7–16, > 16) and needs to include 368 patients per category of NIHSS or 1104 patients in total (software R v3.3.1).

To account for an estimated 5 to 10% of lost to follow-up, it is necessary to include 1210 patients.

#### Statistical analysis

##### Analysis strategy

The analysis of the assessment criteria will be carried out on available data, i.e. without any replacement of missing data. For the analysis of the primary endpoint, a sensitivity analysis of missing data, using a multiple imputation method, may be considered. The analysis will be carried out using the SAS 9.3 software (or later version) considering a risk of first species fixed at α = 5%. A statistical analysis plan will be defined blind data.

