**Cog impairment** using the **French Telephone Interview for Cognitive Status Modified (F-TICS-m).** The TICS scale is a tool for screening for memory disorders. It evaluates time orientation, spatial orientation, immediate memory, calculation, semantic memory, delayed recall, language, understanding of an instruction. Cut offs of 24 and 34 are used (a score less than 24 corresponds to dementia, a score between 24 and 33 corresponds to mild cognitive impairment and a score more than 34 corresponds to a normal condition). This scale was validated in French by telephone [19].**Depression and anxiety** using the **hospital anxiety and depression scale (HADS)**. The anxiety and depression score through the HADS seeks to identify an anxiety-depressive symptomatology and assess its severity. It is composed of 14 items divided into 2 scores of seven items each: a depression score (one for dysphoria, one for deceleration and five for the anhedonic dimension) and an anxiety score. Each item is rated from 0 to 3, allowing to obtain 2 scores. The maximum score for each score is 21. This scale was validated in French by telephone and in a self-administered collection mode [20].**Fatigue** using the **Fatigue Severity Scale (FSS).** The fatigue score through the FSS measures the impact of fatigue on different functions. This is a short questionnaire of nine questions, to which the patient answers on a scale from 1 to 7. The overall score is the average of all the scores obtained on each of the 9 questions. The higher the result, the greater the fatigue. A threshold of 5.5 is often used to differentiate high and low fatigue. This scale was validated in French in a self-administered collection mode [21].**Genito-sexual disorders** using closed-ended question “yes/no”.**Limitations of activities** using the **modified Rankin Scale (mRS)** [23] and the **Barthel Index (BI)** [22]. The modified Rankin Scale (mRS) and the Barthel Index (BI) are commonly used scales measuring the actual abilities of the stroke patient in the basic activities that determine autonomy. The mRS is a more global scale, which measures functional independence rather than the performance of specific tasks. In this way, mental as well as physical adaptations following neurological deficits are assessed. The scale consists of 7 levels, from 0 to 6, with 0 corresponding to no symptoms and 6 corresponding to death. Cut offs of 2 is used (a score less than or equal to 2 corresponds to independence, a score greater than 2 corresponds to dependence). This scale was validated in French by telephone and in self or hetero-administered data collection mode. The IB was developed in 1965 [22] and later modified by Granger and colleagues [43] to measure patient performance in 10 activities of daily living. The IB is considered a sensitive and reliable disability scale for stroke patients. The IB items can be divided into two groups: one, related to self-care (diet, grooming, bathing, clothing, urinary and anal continence, and toilet use) and the other, related to mobility (ambulation, transfers and stair climbing). The maximum score is 100, which indicates that the patient is totally independent in physical functioning. The lowest score is 0, which represents a totally dependent bedridden state. A dependency to consider a return home is usually defined by a score greater than or equal to 60. The IB is a scale validated in French in a data collection mode by interview (hetero-administered).**Participation restrictions** using the **Community Integration Questionnaire (CIQ)**. The CIQ assesses disability for brainy people in three areas: home integration (active participation in the functioning of the home or household), social integration (participation in social activities outside the home), productivity (regular work performance). It is composed of three sub-scores: home integration [0–12], social integration [0–10], productivity [0–7]. The total CIQ score [0–29] is the sum of the 3 sub-scores.

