## Discussion

### Expected outcomes

By integrating a longitudinal dimension and relying on a large cohort, the new knowledge generated by this project will make it possible to identify the barriers and the factors favorable to the outcome of the life pathways, i.e.: 1) information on the elements of the pathway most closely associated with patient functional prognosis, 2) an accurate description of the life pathways, patients with stroke, by defining a typology of these pathways, information currently poorly known, especially on the downstream path, 3) very precise information on the frequency of post-stroke sequelae 3 months and 1 year after the stroke, information currently missing in France.

This information is important for the planning of the offer and thus to the shared and enlightened management of the public policies concerning stroke pathways. Thus, knowledge about the link between the life pathways and functional outcome will bring original information to reduce the impact of stroke by taking into account resources needed meeting the needs of patients and objective information on the inequalities of access to care and on the shortcomings of the healthcare offer.

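### Patients who cannot take the telephone cognitive test drop out under the available-data rule, so the frequency of cognitive disorder may be understated, most in the severe stratum

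*Protocol article*

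**What the plan says.** All references are to the protocol article.

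- **Measurement.** Table 1 (footnote 5) and the section on ad hoc collection of sequelae have the nurse give F-TICS-m by telephone at 3 months and 1 year. The Data sources section lists its domains, which include calculation, delayed recall, language and following an instruction.
- **Proxies.** A caregiver may fill in FSS, HADS and CIQ-R. At inclusion, relatives or the care team may answer for a patient who cannot. No substitute is described for F-TICS-m.
- **Outcome classes.** Evaluation criteria groups the score into three classes: dementia, mild impairment and normal. There is no class for untestable patients or for death.
- **Population.** The selection criteria exclude neither aphasia nor severe deficit. Under Sample size selection the study "needs to include 368 patients per category of NIHSS or 1104 patients in total", so one third of the required patients have discharge NIHSS above 16.
- **Missing data.** Analysis strategy states: "The analysis of the assessment criteria will be carried out on available data, i.e. without any replacement of missing data". A multiple-imputation sensitivity analysis may be considered, and only for the primary endpoint.
- **Deliverable.** Expected outcomes promises "very precise information on the frequency of post-stroke sequelae 3 months and 1 year after the stroke".

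**The concern.** Whether a patient can take F-TICS-m depends on some of the functions that it measures. A survivor who is reached by telephone but has severe aphasia, or cannot cooperate, has no score, and the stated rule then omits that patient from the cognitive endpoint. The loss should be greatest where discharge NIHSS is highest, and the design deliberately enlarges that group.

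Two results are exposed:

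- **Frequency.** The article presents the frequency of sequelae as a main product. If untestable patients are more often impaired, it is understated.
- **Associations with pathway elements.** Speech therapy is one of the elements studied, and the article itself says that severity shapes the pathway. If untestability differs by exposure, the odds ratios can move.

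The random-effects models planned for sequelae use observed scores, so they do not correct for missingness that depends on the unseen score. The optional comparison in the Analysis plan covers patients who died, were lost or withdrew. A patient who was reached but could not be tested is none of these.

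**Working it through.** **1. The plan's own figure.** Inputs from Sample size selection: two-sided 5% (sidedness assumed), power 80%, odds ratio 2, mRS distribution 51/30/19%, exposure a = 20% or 80%. Whitehead's proportional-odds formula gives

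N = 3(1.960 + 0.842)² / [a(1−a)(ln 2)²(1 − Σp³)] = 23.55 / (0.16 × 0.4805 × 0.8335) = 367.5, so 368.

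Three strata give 1104. The sample size is reproduced and is not in question.

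**2. Frequency, all strata equal.** The article gives neither the untestable share nor the prevalence of impairment, so these inputs are assumptions:

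- p = impairment among testable patients: 30/50/70% for NIHSS ≤6, 7–16, >16
- u = untestable share: 2/10/30% (case A) or 5/20/60% (case B)
- all untestable patients are impaired

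Observed = Σ(1−u)p / Σ(1−u). Actual = mean of [(1−u)p + u].

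- Case A: observed (0.294 + 0.450 + 0.490)/2.58 = 47.8%; actual (0.314 + 0.550 + 0.790)/3 = 55.1%.
- Case B: observed (0.285 + 0.400 + 0.280)/2.15 = 44.9%; actual (0.335 + 0.600 + 0.880)/3 = 60.5%.

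Within strata, observed against actual:

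| Stratum | Case A | Case B |
|---|---|---|
| NIHSS ≤6 | 30% v 31.4% | 30% v 33.5% |
| NIHSS 7–16 | 50% v 55% | 50% v 60% |
| NIHSS >16 | 70% v 79% | 70% v 88% |

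**3. Frequency among survivors.** Equal weights ignore deaths. I assume survival s = 95/85/63%. The mean is 2.43/3 = 81%, which matches the 19% deaths assumed in the article. Weighting each term by s:

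- Case A: observed 0.9705/2.137 = 45.4%; actual 1.2635/2.43 = 52.0%; gap 6.6 points.
- Case B: observed 0.7872/1.8345 = 42.9%; actual 1.3827/2.43 = 56.9%; gap 14.0 points.

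**4. Associations.** Take a two-class outcome with a true odds ratio of 2. Let u0 and u1 be the untestable shares among impaired patients, unexposed and exposed. Then observed OR = 2 × (1−u1)/(1−u0).

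| u0 / u1 | Observed OR |
|---|---|
| 20% / 20% | 2.00 |
| 10% / 30% | 1.56 |
| 10% / 50% | 1.11 |
| 30% / 10% | 2.57 |

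For three ordered classes I assume 50/30/20% in the unexposed, with 20 to 60% of the lowest class untestable regardless of exposure. The odds ratio for impaired against normal becomes 1.96 to 1.84. For the lowest class against the rest it stays at 2.00.

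**The case against.** **Failing the test is not the same as being untestable.** A reader might infer that every patient with marked cognitive loss drops out. The article does not support that. The class below 24 exists to register marked loss, so a patient who answers and fails items scores low and stays in. Only patients who cannot take the test at all are missing, and their exclusion is inferred from the collection mode together with the available-data rule. The article does not say how the nurse scores someone who cannot respond. This objection stands, and the point is limited accordingly.

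**Bias in associations is not established.** A reader might infer that associations are biased, or attenuated. Step 4 shows almost no change when untestability among the impaired is equal across exposure, and a shift in either direction when it is not. Stratification on discharge NIHSS and adjustment for other clinical factors should remove part of any difference that is due to severity. This stands too.

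**The sizes are assumed, and equal strata lean high.** This is correct. Allowing for deaths reduces the gaps from 7.3 to 6.6 points and from 15.6 to 14.0, so they do not vanish.

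**The call form and analysis plan are not shown.** They may already hold a reason code or further sensitivity analyses, the collection was piloted, and the lack of a proxy for a cognitive test is expected. This softens the point but does not remove it. The article does not merely leave the matter open: it states a rule for all criteria and names imputation for the primary endpoint alone.

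**Conclusion.** The point holds for one secondary endpoint, and mainly for its frequency. With a telephone-only test, no alternative for untestable patients and no replacement of missing scores, the frequency of cognitive disorder among survivors is understated whenever untestable patients are more often impaired. The shortfall is largest for NIHSS above 16.

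Under the stated assumptions, the observed figure is about 45% against 52%, or 43% against 57%, allowing for deaths. With equal strata it is 48% against 55%, or 45% against 61%. These are illustrations, not estimates, because the article gives no untestable share and no prevalence of impairment.

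For associations, the documents support only that distortion is possible, in an unknown direction, if untestability differs by exposure within NIHSS strata. The primary mRS analysis and the sample size are not affected.

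**What to change.** 1. On the follow-up call form, record why F-TICS-m was not obtained: language or cognitive inability, refusal, not reached, or death.
2. Report untestable because of language or cognition as its own category among survivors, by NIHSS stratum.
3. Pre-specify one sensitivity analysis that places these patients in the lowest F-TICS-m class. Show it beside the available-data result, so that the two serve as bounds.

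The cost is one field on the form and one added analysis. The field has to be in place before the calls are made, because a later analysis plan cannot recover a reason that was not recorded. The downside is that pure aphasia is counted as cognitive impairment in the added analysis, so it should accompany the available-data result and not replace it.

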##### Statistical methods

Qualitative variables will be described in terms of numbers, percentages, and 95% confidence intervals according to the exact binomial distribution. Comparisons will be made by the Chi-square, corrected Chi-square or exact Fisher test. A logistic or polytomial regression model will be used to take into account the adjustment variables.

The quantitative variables will be described in terms of mean, standard deviation, median, extent and interquartile range. Comparisons will be made by Student test, Student test for unequal variances, Wilcoxon test, according to the distribution of the variable of interest.

##### Analysis plan

Characteristics of patients at inclusion and during the study.

Patients will be described to the following variables: compliance with eligibility criteria; socio-demographic, clinical, and pathways characteristics. A description of the violations of the protocol, causes of death and abandonment will be made and patients who have died, lost sight of, or abandoned research may be described and compared with other patients.

Analysis of the primary endpoint.

The mRS, the primary endpoint, is an ordered variable with three response modalities. The analysis is based on a Proportional Odds Model, assuming an identical odds ratio for each possible dichotomization of the criterion.

In order to take into account the correlation between the measurement of the mRS at 3 months and that one at 1 year, a random effect on the time will be systematically added to the models.

The odds proportionality hypothesis and the log-linearity hypothesis will be systematically checked.

Analysis of secondary endpoints
◦ Typology of the different patient stroke pathways

In order to identify the types of paths, a hierarchical clustering, or latent class clustering, will be carried out.
◦ Stroke elements associated with post-stroke sequelae

In order to evaluate the association between the pathway elements and each of the identified sequelae, linear, logistic or polytomic regression models with random effects will be implemented. The assumptions underlying the modelling used will be systematically verified.
◦ Social and geographical inequalities in care

The social and geographical characteristics of the patients included will be described and compared, using the descriptive and comparative statistical methods detailed above, between the different types of pathways identified.

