## Objectives

The main objective of the PAPASéPA project is to identify the life pathways components of stroke patients associated with the activity limitations measured by the Modified Ranking Score (mRS), at 3 months and 1 year after the acute episode.

The secondary objectives are to: 1) identify the life pathways components of stroke patients associated with other types of sequelae (cognitive disorders, anxio-depressive disorders, fatigue, restriction of participation) at 3 months and 1 year after the acute episode; 2) define a typology of the life pathways of stroke patients in Aquitaine, from acute care to 1 year of follow-up and 3) analyze the social and geographical inequalities in the management of stroke in Aquitaine.

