◦ Number / type / duration of hospitalization in medicine or surgery departments, rehabilitation department, psychiatry department and hospitalization at home. Hospitalisations will be classified into three categories corresponding to hospital stays with different clinical meanings with regard to the evolution of stroke (readmission for management of stroke recurrence and post-stroke complications, readjustment for post-stroke follow-up and secondary prevention of stroke and re-hospitalizations to manage a clinical situation not related to stroke);◦ Number / type of medical and paramedical consultations at hospital;◦ Medical ambulatory care: number / type of medical consultations (general practitioner, neurologist, functional rehabilitation physician, cardiologist) and of paramedical consultations (physiotherapy, speech therapy, orthopsy), number of care periods, total duration of each care period;◦ Quantity of drug deliveries (antiaggregant, antihypertensive, statin or anticoagulant treatment, analgesic);◦ Vital status of patients.

**Ad hoc collection** at any of three points in the study (initial episode, at 3 months and 1 year after the initial episode).

The collection time for each variable is specified in Table 1. The categories of variables collected are as follows:
◦ **Clinical data:** risk factors (Alcohol), severity of stroke at discharge (NIHSS)◦ **Stroke life pathways data:** patient referral, level of education, marital status, cohabitation status, professional activity, ability to drive, place of life, participation to a therapeutic education program, medical and social care, allowances for disability, presence of family and caregiver, development and technique to improve autonomy and home care, technical assistance for walking, legal background.◦ **Post-stroke sequelae assessment**

A selection of scales measuring each of the dimensions explored in our project was selected, based on elements of feasibility, frequency of use in the exploration of the dimension considered and metrological performance (validity and reproducibility): The mode of collection of sequelae has been adapted according to the validated mode of administration for each of the scales. The following sequelae are assessed:

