#### Life pathways: perimeter

Despite a collective awareness, as to the inadequacy of the organization of the health system, different realities exist regarding the notion of pathways [38, 44–46].

In the PAPASéPA project, we adopt the global conception of the life pathway of stroke patients. All the elements of care but also the context of life in which the patient evolves (family and social environment, financial aid, income, adaptation of lifestyle and environment, etc.…) will be taken into account.

However, life pathway data are mainly collected during phone interviews using closed-ended questions. Responses may lack of precision and could be not exact. In order to obtain a more precise description of these life pathways access to databases such as the CDAPH (Commission for the rights of disabled persons to independence) would be necessary. This database, which collects all the social benefits people receive, will only be available in the coming years.

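### By the protocol's own definitions, social characteristics are part of the life pathway that is clustered and are then tested between the resulting types, so the social half of the inequality analysis can be circular

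*Protocol article*

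**What the plan says.** All references are to the protocol article.

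- **Objectives.** Secondary objective 2 is to "define a typology of the life pathways of stroke patients in Aquitaine, from acute care to 1 year of follow-up". Secondary objective 3 concerns social and geographical inequalities in stroke management.
- **Data sources.** The ad hoc collection is itemised as "Stroke life pathways data: patient referral, level of education, marital status, cohabitation status, professional activity", followed by driving, place of life, care, allowances and other items. Table 1 puts the same social items under its stroke-pathway heading.
- **Life pathways: perimeter.** The project adopts a global view of the pathway that covers care and also "the context of life in which the patient evolves (family and social environment, financial aid, income", among other elements. The Background section on stroke life pathways likewise includes family and social environment and resources.
- **Analysis plan, typology.** To find the types, "a hierarchical clustering, or latent class clustering, will be carried out". The input variables are not named.
- **Analysis plan, inequalities.** "The social and geographical characteristics of the patients included will be described and compared, using the descriptive and comparative statistical methods detailed above", and this is done "between the different types of pathways identified".
- **Statistical methods.** The methods referred to are chi-square or Fisher tests, t or Wilcoxon tests, and logistic or polytomous regression where adjustment is needed.

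**The concern.** A test of a variable between groups assumes that the groups were formed without using that variable. Clustering places patients who are alike on its inputs in the same group, so an input tends to differ between clusters even when it is unrelated to everything else. If education or cohabitation status is among the inputs, a significant difference in it between types may only reflect how the types were made.

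Secondary objective 3 is at stake. The Discussion (Expected outcomes) promises objective information on unequal access to care for public policy. A circular comparison could supply a finding of social inequality that the data do not contain.

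A smaller point concerns severity. Recruitment fills a quota in each discharge-NIHSS stratum, and the protocol says severity influences the type of pathway. Differences between types will therefore partly reflect case-mix unless severity is adjusted for.

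**Working it through.** **1. Do the same variables stand on both sides?**

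| Step | Section | Content |
|---|---|---|
| Object clustered | Objectives; Analysis plan | Life pathways, acute care to 1 year |
| Life-pathway data | Data sources; Table 1 | Include education, marital status, cohabitation, professional activity |
| Scope of the pathway | Life pathways: perimeter | "family and social environment, financial aid, income, adaptation of lifestyle and environment" |
| Variables tested between types | Analysis plan | Social and geographical characteristics |
| Variables excluded from clustering | none | None stated |

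An analyst following these definitions would cluster on the social variables and then test them. Place of residence differs: Data sources lists it with date of birth and sex as socio-demographic. It is also distinct from place of life (home, institution, medico-social structure), which is pathway data.

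**2. Sample size used.** The protocol gives no figure for the typology or for objective 3. The simulations use its primary-analysis size, which reproduces with the proportional-odds formula (outcome 51/30/19%, odds ratio 2, exposure 20% or 80%, two-sided 5%, power 80%):

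N = 3(1.960 + 0.842)² / [0.2 × 0.8 × (ln 2)² × (1 − 0.51³ − 0.30³ − 0.19³)] = 367.5, so 368 per stratum and 3 × 368 = 1104 in total.

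This only fixes N; it says nothing about circularity.

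**3. Size of the effect if social variables are clustered.** Assumptions not in the protocol: binary standardised variables, Ward hierarchical clustering, four social variables generated independently of care, and a 5% chi-square test of each between clusters.

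*(a) No true types in the care data* (N = 368 or 1104; 3, 4 or 6 clusters; 10 or 20 care variables; 200 or 60 simulated cohorts per setting). Rejection rate per social variable:
- social variables clustered: 48% to 91%
- social variables left out: 2.5% to 7.5%

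*(b) Four true care types* (N = 1104, 4 clusters, 12 care variables, 80 cohorts). Each care item has log-odds +s or −s by type, so its probability is 1/(1 + e^−s) or the complement.

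| s | Item probabilities | Clustered | Left out |
|---|---|---|---|
| 0.5 | 0.62 / 0.38 | 95.3% | 5.6% |
| 1.0 | 0.73 / 0.27 | 78.1% | 5.6% |
| 1.5 | 0.82 / 0.18 | 25.6% | 3.4% |
| 2.5 | 0.92 / 0.08 | 8.4% | 5.3% |

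**4. Simulation error.** Each cell in (b) rests on 80 × 4 = 320 tests. The standard error at 5% is √(0.05 × 0.95 / 320) = 1.2 percentage points, so the left-out column agrees with 5%. In the last row the gap is 8.4 − 5.3 = 3.1 points, with standard error √[(0.084 × 0.916 + 0.053 × 0.947) / 320] = 2.0 points. With very sharply separated types the inflation is therefore small and not clearly established. In the other three rows it is beyond doubt.

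**The case against.** The strongest reply is that the protocol never says social variables enter the clustering. The inputs are not listed, a separate statistical analysis plan is announced, and several places suggest a narrower typology:

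- Study design names pathway data and socio-economic and environmental data as different things.
- The description of patients in the Analysis plan separates socio-demographic, clinical and pathway characteristics.
- The section on the evolving character of events separates the socioeconomic environment from health events.
- Outlook describes reconstructing pathways by linking successive hospital stays, which would bring in no social variables.
- Education and professional activity are recorded only at inclusion, so they are not obvious parts of a trajectory running from acute care to 1 year.

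This stands to the extent that entry of the social variables is an inference. It does not dispose of the point. The explicit classification in Data sources and Table 1, and the global scope in Life pathways: perimeter, point the other way. If the Outlook account governs, objective 2 is not a typology of life pathways as the protocol defines them. If the global definition governs, objective 3 is circular. That is a conflict within the document, not detail left to a later plan.

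Two further replies are sound. Statistical methods already provides regression for adjustment, and the justification of the study design names discharge NIHSS as a major potential confounder, so the severity point asks only that this be applied here. Adjustment does not cure circularity, however. And the geographical comparison, so far as it rests on place of residence, is not circular by definition.

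**Conclusion.** The point holds conditionally. On the protocol's own definitions the social comparison for secondary objective 3 uses variables that belong to the clustered object, with no exclusion stated. On that reading its p-values are invalid and it can show social differences that are not there.

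Under the assumed settings the false-positive rate per social variable is about 8% to 95% if the variables are clustered and about 5% if they are not. The range depends mainly on how sharply care separates the types, which is unknown in advance. Latent class clustering, the protocol's alternative, was not simulated.

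A reader might infer more: that social variables certainly form the typology, that differences will necessarily be found, or that the whole inequality analysis fails. The documents do not support this. The inputs are unlisted and a narrower reading exists, inflation is small when types are very distinct, and place of residence lies outside the life-pathway data.

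**What to change.** Reconcile Data sources and Life pathways: perimeter with Outlook, and state the clustering inputs. For objective 3:

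1. Build the typology from care and service-use components only (for example referral, hospital stays, rehabilitation, consultations, support services).
2. Keep education, occupation, marital and cohabitation status, income proxies and residence outside the clustering, as external comparison variables.
3. Compare them across types with the regression model already named in Statistical methods, including discharge NIHSS as an adjustment variable.
4. If a full life-pathway typology is wanted for objective 2, keep it as description and do not test its own input variables between its types.

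The cost is wording in the analysis plan and one extra clustering run, with no new data or patients. The drawback is having two typologies to present and explain. Analysis strategy says the statistical analysis plan is still to be defined on blind data, so the change can be made before results are seen.
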